## Abstract

**Background:**

Pancreatic cancer patients’ prognosis may be limited by two conditions, cachexia and sarcopenia. Resistance exercise and protein supplementation are safe non-pharmacological strategies that may increase or preserve skeletal muscle mass within this population. Therefore, the primary aim of this study is to examine the feasibility of a home-based virtually supervised resistance exercise intervention, with or without protein supplementation in pancreatic cancer patients initiating neoadjuvant chemotherapy. This intervention may also maintain skeletal muscle mass and improve plasma biomarkers associated with muscle tissue wasting, physical function and psychological measures.

**Methods:**

We aim to recruit 45 patients with locally advanced pancreatic cancer initiating neoadjuvant chemotherapy. Patients will be randomized to receive either Resistance Exercise (RE) (n = 15), Resistance Exercise and Protein Supplementation (RE + PS) (n = 15), or Attention Control (AC) (n = 15). Patients randomized to RE or RE + PS will receive 16-weeks of home-based virtually supervised resistance exercise. The AC will receive a 16-week stretching program. Primary and secondary outcomes will be measured at baseline and after 16 weeks during study visits.

**Discussion:**

The REBUILD trial is the first randomized controlled trial that combines resistance exercise with daily protein supplementation during neoadjuvant chemotherapy in pancreatic cancer patients. Our novel home-based virtually supervised exercise intervention seeks to mitigate barriers to participation in this vulnerable population. Furthermore, results of this trial will address important research gaps associated with pancreatic cancer-related cachexia, a condition closely connected with poor prognosis and mortality.

## Introduction

Pancreatic ductal adenocarcinoma is one of the most fatal and aggressive cancer diseases, with an estimated 5-year survival rate of 13%. [1] Pancreatic cancer is projected to become the second leading cause of cancer death by 2030 in the U.S., given the demographic shift towards an increasingly aging population. [2] The current standard of care in patients with resectable pancreatic ductal adenocarcinoma is surgery and systemic chemotherapy. However, chemotherapy and the disease itself can induce muscle wasting and weakness leading to a diagnosis of cachexia and/or sarcopenia. [3] Cachexia is a tissue-wasting syndrome characterized by severe weight loss, typically defined as an unintended loss of more than 10% of pre-illness stable weight. [4] Sarcopenia, on the other hand, involves the progressive loss of skeletal muscle mass, strength, and function. [5] Both conditions are associated with reduced physical function, poor responses to treatment, and decreased survival rates among patients with pancreatic ductal adenocarcinoma. [6–9] Nonetheless, no systemic strategies are provided in current standard of care to prevent potential muscle wasting for patients with pancreatic cancer.

Resistance exercise and protein supplementation are safe non-pharmacological strategies that may increase or preserve skeletal muscle mass in various cancer settings, with most evidence in prostate cancer [10,11] and breast cancer. [12–14] Indeed, resistance training is recommended as an essential component for sarcopenia and cancer cachexia treatment. [10,15] While aerobic exercise provides substantial cardiovascular and systemic benefits, it is less effective in directly addressing sarcopenia related outcomes. [10,15] Pancreatic cancer patients are largely underrepresented in exercise and nutrition interventions. Exercise-induced benefits in pancreatic cancer patients have been previously reported for increasing physical activity participation, physical function, and quality of life, [16,17] with preliminary efficacy in improving skeletal muscle mass in case report studies. [18–20] The addition of protein supplementation is strongly associated with muscle mass maintenance or improvement in frail non-cancer populations. [21] Although numerous investigations support the use of post-exercise protein supplementation to enhance acute muscle protein synthesis in non-cancer population, [22] limited data attest to the long term effects of protein supplementation and resistance exercise with regards to its feasibility and effectiveness on skeletal muscle mass within the pancreatic cancer population. [18]

Thus, the ongoing REBUILD trial is a three-armed pilot randomized controlled trial designed to evaluate the feasibility of a home-based virtually supervised resistance exercise intervention, with or without protein supplementation, in pancreatic cancer patients initiating neoadjuvant chemotherapy. Our secondary aim is to examine the effects of home-based virtually supervised resistance exercise combined with or without protein supplementation on skeletal muscle mass, plasma biomarkers associated with muscle tissue wasting, physical function and psychosocial measures. We hypothesize that a home-based virtually supervised resistance exercise intervention with or without protein supplementation will be feasible, with at least 70% of exercise sessions completed and protein supplementation consumed among pancreatic cancer patients undergoing neoadjuvant chemotherapy. Furthermore, we hypothesize that a home-based virtually supervised resistance exercise combined with protein supplementation will elicit greater maintenance of skeletal muscle mass and improvements in plasma biomarkers associated with muscle wasting compared with resistance exercise alone and attention controls. Lastly, we hypothesize that resistance exercise alone or in combination with protein supplementation will improve physical function and psychosocial measures when compared to attention controls.

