#### 2.6.1. Primary outcome.

*2.6.1.1. Feasibility*

Feasibility of the RE intervention The intervention is considered feasible if 1) patients attend ≥70% of the total prescribed number of exercise sessions (dependent on their treatment duration) [17,32] and 2) **≥**70% of sessions completed at the planned prescription (i.e., relative dose intensity ≥ 100%). The planned exercise volume (sets x reps x weight) is established prior to exercise session with the %1RM weights calculated from 10RM testing at baseline. However, in the event estimated 1RM is not available or the patient is not being adequately progressed during the intervention (i.e., weights become to easy to move relative to intended %1RM intensity), the lead exercise trainer would prescribe the highest tolerable weight based on pre-determined volume (sets x repetitions). A dose modification is defined as a reduction in sets, repetitions, and/or weight during the session that deviated from the planned volume, whereas a dose escalation is defined as an increase in sets, repetitions, and/or weight. Both dose modification and escalation were applied during the session at the discretion of the exercise trainer and reported as actual volume completed. Planned and actual volume for each resistance exercise were respectively calculated and summed to derive total planned and actual prescribed volume for each session, which were summed to obtain total planned and actual intervention volume. Exercise relative dose intensity is then calculated as the ratio of total actual resistance volume to total planned resistance volume. Reasons for missed sessions are documented throughout the study. [33] To account for missed sessions due to illness, family and work obligations, patients are given 6 exercise sessions to make-up at the end of their program if their treatment timeline permits. Feasibility of the RE ± PS intervention: The same criteria described above are used for the exercise portion. Additionally, patients are considered compliant and the PS intervention feasible if they consume ≥70% of the total prescribed doses of protein supplementation. Protein adherence is captured for the RE + PS group by asking patients during the supervised exercise sessions if they have been compliant with protein supplementation intake and recording on the exercise sessions data sheet.

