### 2.9. Sample size calculation

We plan to recruit 45 patients (n = 15 per group). This sample size was determined based on recommendations of samples sizes between 24 and 50 for feasibility studies for assessing the feasibility of the intervention and estimating effect sizes for designing future studies. [61–63] The primary endpoint of this study is feasibility of the resistance exercise combined with protein supplementation intervention. When the sample size n = 15 in the resistance exercise combined with protein supplementation group and the true feasibility rate of 85%, we can observe a feasibility rate ≥70% with the probability of 82%.

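### The primary feasibility endpoint is stated as a 70% share of sessions or doses and also as a proportion of patients, and nothing links the two

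*Protocol article*

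**What the plan says.** - **Introduction (hypothesis).** The intervention will be feasible "with at least 70% of exercise sessions completed and protein supplementation consumed among pancreatic cancer patients undergoing neoadjuvant chemotherapy". This is a share of sessions and of protein. No share of patients is given.
- **Section 2.6.1.** The intervention counts as feasible if two exercise conditions hold: "patients attend ≥70% of the total prescribed number of exercise sessions", and at least "70% of sessions completed at the planned prescription". For the protein arm the same exercise conditions apply and a third is added: "patients are considered compliant and the PS intervention feasible if they consume ≥70% of the total prescribed doses of protein supplementation". That one clause covers both a patient's compliance and the intervention's feasibility.
- **Section 2.9.** The calculation is set up as "When the sample size n = 15 in the resistance exercise combined with protein supplementation group", takes "the true feasibility rate of 85" per cent, and concludes that "we can observe a feasibility rate ≥70" per cent with probability 82%.
- **Section 2.10.** The primary analysis population is all randomized patients. The primary endpoint, feasibility of RE + PS, gets a point estimate and an exact 95% confidence interval from that arm's patients. No success rule is given.

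**The concern.** An exact binomial interval and a feasibility rate out of 15 make sense only if each patient is scored yes or no. The Introduction and Section 2.6.1 attach the word feasible to something else, the 70% share of sessions or doses. Because 70% appears at both levels, it is easy to slide from one to the other without noticing that the quantity has changed.

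At stake is the trial's primary conclusion. Section 2.4 says interventionists and outcome assessors are not blinded, and Section 2.8 reports patients who have already finished the intervention. If the rule stays open, it could be settled after adherence has been seen. The sample-size statement also supports only the patient-level version.

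**Working it through.** **Inputs.** From Section 2.9: n = 15, true rate 85%, observed rate at least 70%, stated probability 82%. From the Introduction and Section 2.6.1: 70% of sessions or doses. From Section 2.5.1.1: 3 sessions a week for at most 16 weeks, so 3 × 16 = 48 sessions. The attendance patterns below are constructed to test the two readings; they are not forecasts.

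**1. The plan's own figure.** Let X be the number of feasible patients, X ~ Binomial(15, 0.85). At least 70% of 15 is 0.70 × 15 = 10.5, so at least 11 patients.

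| Rule | Observed share | Probability |
|---|---|---|
| X ≥ 10 | 66.7% | 98.3% |
| X ≥ 11 | 73.3% | 93.8% |
| X ≥ 12 | 80.0% | 82.3% |
| X ≥ 13 | 86.7% | 60.4% |

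The stated 82% is not reproduced at the stated threshold. It matches only X ≥ 12, an observed share of at least 80%. A normal approximation at 10.5/15 gives 94.8%, and changing n from 10 to 20 under a 70% rule gives 88.2% to 97.8%, so neither explains it. The match at 12 of 15 does show that Section 2.9 treats feasibility as a proportion of patients.

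**2. The two readings on the same data (attendance only, equal treatment duration).** Session share = mean of the patients' attendance. Patient share = number at 70% or more, divided by 15.

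- 10 patients at 95%, 5 at 40%: sessions (10 × 0.95 + 5 × 0.40)/15 = 11.5/15 = 76.7%; patients 10/15 = 66.7%.
- 11 patients at 72%, 4 at 10%: sessions (11 × 0.72 + 4 × 0.10)/15 = 8.32/15 = 55.5%; patients 11/15 = 73.3%.

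**3. The same in whole sessions, 15 × 48 = 720 in all.** Reaching 70% takes 34 of 48 (70.8%), since 33 of 48 is 68.8%.

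- 9 patients at 46 and 6 at 20: (414 + 120)/720 = 534/720 = 74.2% of sessions; 9/15 = 60% of patients (exact 95% interval 32% to 84%).
- 11 patients at 34 and 4 at 8: (374 + 32)/720 = 406/720 = 56.4% of sessions; 11/15 = 73.3% of patients (exact 95% interval 45% to 92%).

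**4. How far apart the readings can be.** With 10 of 15 patients reaching 70%, pooled attendance can be as high as (10 × 48 + 5 × 33)/720 = 645/720 = 89.6%. With 11 of 15, it can be as low as 11 × 34/720 = 374/720 = 51.9%.

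**The case against.** The strongest reply is that a nested reading is natural: 70% within a patient, then a proportion of patients. Section 2.6.1 makes the number of prescribed sessions depend on the patient's own treatment duration and speaks of compliant patients, and Sections 2.9 and 2.10 follow on from there. The hypothesis in the Introduction is one sentence and mentions no pooling or averaging. This carries weight. The nested reading is probably what is meant and is the one to adopt. But no section states it, and the Introduction and Section 2.6.1 apply the word feasible to the intervention at the session or dose share itself.

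Three stronger readings are tempting and are not supported:

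- *That the plan contains two formal decision rules in conflict.* Section 2.9 gives the chance of observing a rate of at least 70%, and Section 2.10 plans estimation only. A patient-level go/no-go rule is not written, so the examples show disagreement against the 70% mark, not breach of a stated rule.
- *That the three criteria are left uncombined.* Section 2.6.1 joins the two exercise conditions and adds the protein condition for RE + PS. What is missing is the step from a patient's result to the trial's result.
- *That 85% applies to each criterion, so the combined rate must be much lower.* Section 2.9 assigns 85% to the feasibility rate itself. No section gives component rates or supports independence. Protein intake is asked about at the supervised sessions, so recorded adherence to the two may well be correlated.

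An analysis plan that is not shown may add detail. It would not remove the mismatch between sections of this article on what the primary endpoint is.

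**Conclusion.** The point holds as an unlinked definition of the primary endpoint. On the same data, the session share and the patient share can fall on opposite sides of 70% in both directions: 76.7% against 66.7%, and 55.5% against 73.3%. This rests on attendance alone, equal treatment durations and constructed patterns. It shows that the readings can diverge, not how likely that is. Reporting the proportion with its interval would limit the harm, provided it is settled in advance which proportion that is.

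Separately, the threshold and probability in Section 2.9 do not agree: at least 70% of 15 gives 93.8%, and 82% belongs to at least 80%. This follows from the stated n and true rate with no further assumption beyond independent patients.

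**What to change.** Use one definition in the Introduction and in Sections 2.6.1, 2.9 and 2.10:

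1. A RE + PS patient is compliant if all the Section 2.6.1 criteria are met: attendance, sessions at the planned prescription, and protein doses.
2. Feasibility is the proportion of randomized RE + PS patients who are compliant, reported with its exact 95% confidence interval.
3. The 85% planning rate refers to this combined endpoint.
4. Pooled session and dose shares, and each criterion alone, are reported descriptively.
5. In Section 2.9, either keep at least 70% (at least 11 of 15) and print 93.8%, or keep 82% and print at least 80% (at least 12 of 15). If the sponsor wants a success rule, state the deciding count in Section 2.10 as well.

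The cost is wording and one recalculated probability. Sample size and data collection do not change. The downside is that requiring all criteria in the same patient cannot give a higher rate than the weakest single criterion. The choice should be fixed and dated before adherence in the arm is summarised.

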## 2. Materials and methods

### 2.1. Study design

The REBUILD trial is a single-center, three-armed, pilot randomized controlled trial (RCT) underway at Dana-Farber Cancer Institute (DFCI), Boston, Massachusetts. A total of 45 patients with locally advanced pancreatic cancer initiating FOLFIRINOX or gemcitabine/abraxane neoadjuvant chemotherapy are recruited from the Dana-Farber Gastrointestinal Cancer Center and randomized to either receive Resistance Exercise (RE) (n = 15), Resistance Exercise and Protein Supplementation (RE + PS) (n = 15), or Attention Control (n=15) (AC). The intervention groups participate in a home-based virtually supervised resistance exercise program three days per week with or without protein supplementation over the course of neoadjuvant chemotherapy (maximum 16-weeks). The intervention period was set at maximum 16 weeks to align with the common duration of the neoadjuvant chemotherapy prior to surgery in this population. The AC group receives a stretching program over the course of neoadjuvant chemotherapy and is offered the RE + PS program following completion of treatment and may begin the intervention within and up to 6 months post-surgical resection. Outcome measures are tested at baseline and within one week of intervention completion. Approval of the trial protocol was obtained from the DFCI Institutional Review Board (IRB# 21–506). Any amendments made are communicated to all appropriate authorities. This clinical trial is registered in ClinicalTrials.gov (NCT05356117).

### 2.2. Eligibility criteria

To be eligible to participate in this study, patients must meet the following inclusion criteria: 1) are ≥ 18 years of age, 2) non-metastatic pancreatic cancer initiating neoadjuvant chemotherapy, 3) speaks English or Spanish, 4) able to provide physician clearance to participate in the exercise program, 5) able to initiate a supervised exercise program, 5) currently participates in less than 60 minutes of structured moderate or vigorous exercise per week, 6) non-smoker (no smoking during previous 12 months), and 7) willing to travel to DFCI. Key exclusion criteria include: 1) metastatic disease, 2) uncontrolled illness including active infection, diabetes, hypertension, or thyroid disease, 3) history of musculoskeletal, cardiorespiratory, or neurological diseases that preclude the participation in moderate intensity exercise, 4) receiving other investigational agents and or other cancer directed treatments, 5) other active malignancies, and 6) regularly consuming protein supplementation.

### 2.3. Recruitment and screening

Patients are recruited through various recruitment strategies at the DFCI and regional site clinics. For potential patients identified through patient lists, we contact their medical oncology providers, and request permission to contact the patients to invite them to participate in the study. Potentially eligible patients are further screened by study staff by phone to confirm eligibility, which includes a short questionnaire to determine eligibility and completion of the Godin Leisure Time Questionnaire [23] to assist in determining the patient’s current exercise level. To confirm the patient’s health status and how this relates to undertaking an exercise program we use the Physical Activity Readiness Questionnaire. [24] Interested patients are then scheduled for a consent visit with a member of the study staff where we review the protocol and confirm interest by signing informed consent, either in person or electronically using e-consent. To successfully recruit and retain pancreatic cancer patients in an exercise clinical trial we employ several strategies including follow-up phone calls/emails after every visit, informative study brochures, randomization group flyers summarizing what to expect after testing, scheduling flexibility for testing or exercise training appointments, home-based virtually supervised exercise sessions, and transportation support resources (e.g. parking voucher, reimbursement for travel expenses, etc.).

### 2.4. Randomization and blinding

Upon completion of baseline testing, patients are randomly assigned to either RE, RE + PS or AC groups in an equal allocation ratio (1:1:1) using a permitted block design with varying block size. The study biostatistician ([name]) prepared the randomization schema prior to trial start-up, and the randomization allocation was provided to staff via a web-based application (REDCap). Study investigators are blinded to the randomization process. The intervention allocation is not blinded to the study patients, interventionists, and outcome assessors due to the nature of exercise intervention.

### 2.5. Intervention

#### 2.5.1. Exercise intervention.

*2.5.1.1. Resistance exercise group (RE):*

The exercise intervention is home-based virtually supervised via Zoom. Patients complete three sessions per week for the duration of their neoadjuvant chemotherapy treatment with a maximum intervention duration of 16 weeks. The RE prescription consists of 2–3 sets of 8–12 repetitions at 70–85% estimated one-repetition maximum (1-RM) and/or at a rate of perceived exertion (RPE) of 6–7 on the Borg 10-scale. Session duration is approximately 60 minutes. Planned prescribed weight was calculated as a percent of estimated 1RM, which was tested at baseline via 10RM for each exercise. Initially, the weight was set at 70% of 1RM and increased by 5% every 2 weeks until week 8, reaching 85% of 1RM. From week 9 to 16, the prescribed weight increased where the highest tolerable weight for the intended repetitions and sets was used to gradually progress the weight. In the event a patient was not able to follow a linear progression due to injury or treatment-related side effects, the highest tolerable weight for the intended repetitions and sets was used. Exercises include chair squat, floor chest press, glute bridge, seated bent over row, lunges, and shoulder press. Exercises are tailored to the patients where the use of alternative exercises targeting similar muscle groups are incorporated depending on the health and physical status of the patients. Each exercise session begins with a 5-minute functional movement-based warm up and culminates with 5 minutes of stretching and 2 core exercises. Patients randomized to this group are provided with handheld weight-adjustable dumbbells and resistance bands. Patients keep all the exercise equipment after the intervention. Furthermore, an automated blood pressure cuff may be provided if study staff deem it necessary for patients’ safety.

*2.5.1.2. Resistance exercise combined with protein supplementation group (RE + PS):*

The same RE intervention described above is prescribed to the RE + PS group. Patients additionally receive and are asked to consume 40g per day of protein (Unjury, Middletown, CT) equating to 2 scoops of protein supplement, [25] aiming to increase their overall protein intake to 1.2–1.5 g/kg of ideal body weight per day, to align with the current protein intake guidelines for adults with chronic diseases and to maximize stimulation of skeletal muscle protein synthesis. [26] On the day of exercise (3 days per week) the patients are asked to consume the protein supplement immediately (within 30 minutes) after exercise. This has been reported as the optimum time to consume protein to enhance muscle protein synthesis. [21,27,28] Timing of protein supplementation intake on non-exercising days (4 days per week) is not dictated, although patients are recommended to consume the 40g dose with a meal, or over two meals (e.g., 20g at breakfast and 20g at lunch), and record time(s) of day consumed. [29] Patients are provided the protein supplement and a shaker bottle with recommendations on how the protein supplement may be prepared and consumed (e.g. with water, milk.).

*2.5.1.3. Attention control group*

This group performs a home-based program of the same stretches utilized in the two intervention groups. The stretching protocol consists of one set of 3–4 static stretching exercises held for 30 seconds and performed 3 days/week. As flexibility exercises are low intensity, low impact and low-volume, minimal caloric expenditure is expected to be incurred. To increase compliance [30] and aid in the standardization of the home-based stretching, [31] patients are provided a booklet of the flexibility exercises. Patients are shown how to use the booklet and instructed in the stretching exercises by study staff prior to the intervention. In addition, patients are asked to complete weekly records of flexibility compliance and physical activity performed outside the study. This group is offered the RE + PS intervention after their treatment period and may start anytime within and up to a time of 6 months post-surgery date. Given the intervention length is dictated by treatment, we offer an intervention that matches the length of the neoadjuvant chemotherapy regime they received during the initial intervention period up to a maximum of 16 weeks. Patients are offered the choice of daily protein supplement if they elect to partake in the RE intervention.

